### Data Storage

All data will be stored in the password-encrypted servers. Upon completion of the survey, all data will be exported to a password protected desktop computer at Kyoto University Department of Global Health and Socio-Epidemiology. Persons not part of the research team will not have any access to the collected data.

### Incentive

A lottery draw at baseline with a 1:100 chance of receiving US $20 will be given to all participants at the end of data collection as an incentive for their time in taking part in this trial. This amount was chosen carefully not to cause undue influence to the target population in that it is not excessive and is fair considering the country’s socioeconomic status.

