### Sampling Method

To recruit participants, we will post a targeted (based on our inclusion criteria), clickable banner advertisement on Facebook. After clicking on the advertisement, potential participants will be redirected to our website. Those who meet our eligibility criteria and have granted informed consent will be sent a unique trial verification code via text message and email. This unique trial verification code will be used to take our survey. Moreover, participants eligible for this trial will be entered into a lottery draw with a 1:100 chance of receiving US $20.

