The goal of the game is to maintain relationships with the characters, while staying healthy and happy. Once all the interactions with the characters have been completed, the game will give feedback on choices made and the risks those choices might carry. The game is expected to have an immense appeal to the youth, as an exciting new way to use their smartphones (see Figure 2 for the actual SwaziYolo screenshots). Participants in the wait-list control condition will complete the baseline and the immediate posttest measures as those in the SwaziYolo intervention condition, but will not play the game until the post-intervention assessment.

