### Sample Size Calculation

The trial will be powered on the primary outcome measure and based on comparison of the change in HIV risk perception score from pre- to post-intervention assessment in the intervention group at 4 weeks. A study conducted in Uganda estimated mean HIV risk perception of M=3.27, SD *=* 1.03, therefore, we used this estimation as our baseline mean and SD to calculate our effect size [21]. Assuming a moderate effect size of 0.477 (identified by Chu et al [22]), alpha (two-tailed)=0.05, beta=0.20, with 1:1 allocation ratio between both groups, and a SD of the outcome in the population of 1.03, the total sample required to sufficiently power the study would be 146 (73 for each group). Moreover, assuming a 30% loss to follow-up rate [15], we then inflated the sample by 30% to yield a sample of 190. After that, we considered gender differences and once more inflated the sample by a factor of 2 to give a final sample size of 380. Finally, to ensure a balance between males and females in both groups we will recruit 190 females and 190 males. The sample size was calculated using Web-based sample size calculation software [23,24].

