#### Primary Outcome Measure: HIV Risk Perception Score

First, we will use bivariate analysis to calculate the mean between baselines and follow-up. Next, to estimate the difference between the 2 groups, we will calculate the difference between the mean change of the intervention group and the mean change of the wait-list control group using two-sample paired *t* test. We will not perform interim analysis.

Secondly, in the case that, even after randomization, we observe some baseline differences, we will use multiple linear regression to adjust for those differences; where the outcome will be the follow-up score and the independent variables will be the intervention group, baseline scores, age, gender, marital status, level of education employment status, current monthly income, and number of times players played SwaziYolo. We will present our results in standardized regression coefficients for the intervention effect on the outcome variable as previously done for this type of hypothesis [25].

Although great effort will be put to minimize attrition, it is common for eHealth trials to typically have substantial attrition [26]. For this reason, our primary outcome analysis will prioritize analysis of the subjects who adhered to their group assignment and were sufficiently exposed to the intervention. Therefore, both pre-protocol analysis (as treated analysis) as well as intention to treat analysis will be done and both results will be reported. The approach of conducting both “intention to treat analysis” together with “as treated analysis” has been observed in literature for example, Weinstein and colleagues [33] followed this approach in their randomized trial comparing surgical versus nonoperative treatment for lumbar disk herniation.

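### The plan allows for 30% loss, but its lottery does not encourage week-4 completion and its analysis answers attrition by favouring adherers, so bias of unknown size and direction is possible

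*Protocol article*

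**What the plan says.** All references are to the protocol article.

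- **Expected loss.** Sample Size Calculation: "assuming a 30% loss to follow-up rate [15], we then inflated the sample by 30% to yield a sample of 190". That figure is then doubled to 380.
- **Outcome timing.** Primary Outcome Measure sets the perceived-risk scale (PRHS) at baseline and at 4 weeks, with no other follow-up.
- **Incentive.** Sampling Method: "participants eligible for this trial will be entered into a lottery draw with a 1:100 chance of receiving US $20". The Incentive section reads: "A lottery draw at baseline with a 1:100 chance of receiving US $20 will be given to all participants at the end of data collection".
- **Control access to the game.** Description of the Intervention says that controls complete the same measures "but will not play the game until the post-intervention assessment". Randomization says that participants are not blinded.
- **Retention effort.** Four-Weeks Follow-Up Data Collection provides for tracing by phone and text of anyone who misses week 4, in either arm.
- **Analysis.** Primary Outcome Measure: HIV Risk Perception Score compares mean change between arms. If baseline differences appear, it uses a linear regression "where the outcome will be the follow-up score". The section gives attrition as the reason for prioritising participants who adhered and were sufficiently exposed. An intention-to-treat analysis is also reported.

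**The concern.** Three features act on the same 114 or so people.

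First, the only monetary incentive is not aimed at the one assessment that carries the primary outcome. On either timing, someone who never returns keeps the same chance as someone who answers.

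Second, the two arms do not face week 4 in the same position. Everyone knows their allocation. Controls are about to gain the game, while intervention participants already have it. Willingness to answer could therefore depend on arm and, within the intervention arm, on whether the person kept playing.

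Third, both primary methods need a week-4 score, and the article's analytic response to attrition is to select further on behaviour after randomisation. If those who are lost changed differently from those who stayed, the between-arm difference among those analysed need not equal the difference among those randomised. A larger sample does not remove that.

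**Working it through.** **1. The plan's own figure.** Inputs from Sample Size Calculation: difference 0.477, SD 1.03, two-sided alpha 0.05, power 0.80, 1:1 allocation.
- n per group = 2 × [1.03 × (1.960 + 0.842) / 0.477]² = 73.2. The plan states 73 per group, 146 in total, so this agrees when 0.477 is read as a raw difference.
- 146 × 1.30 = 189.8, giving 190. Then 190 × 2 = 380. Both are reproduced.

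**2. Who would have a week-4 score.**
- Lost: 0.30 × 380 = 114. Remaining: 266, or 133 per arm.
- Power at 133 per arm: Φ(0.477 / (1.03 × √(2/133)) − 1.96) = Φ(3.78 − 1.96) ≈ 0.965. The issue is bias and not overall power.

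**3. Lottery.**
- Expected value per person: 0.01 × US $20 = US $0.20.
- Prizes: 380 / 100 = 3.8, so about 4 (US $76 to 80).

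| Section | Who is entered | When | Depends on week 4? |
|---|---|---|---|
| Sampling Method | Those eligible | Not stated | No |
| Incentive | All participants | Both at baseline and at the end of data collection | No |

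**4. Possible bias, under assumed values.** The article gives no loss by arm and no difference between lost and retained participants, so both are assumptions here. Let f_I and f_C be the proportions lost in the intervention and control arms. Suppose that the lost change k SD less than the retained, with the same k in both arms. Each arm's mean over all randomised is then its completer mean minus f × k SD, so

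bias = (f_I − f_C) × k SD.

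| Loss, intervention / control | k = 0.25 | k = 0.5 | k = 1.0 |
|---|---|---|---|
| 30% / 30% | 0 | 0 | 0 |
| 35% / 25% | 0.025 SD | 0.05 SD | 0.10 SD |
| 40% / 20% | 0.05 SD | 0.10 SD | 0.20 SD |

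- At 40%/20% with k = 0.5, 0.10 SD is 0.10 × 1.03 = 0.103 points, and 0.103 / 0.477 = 22% of the planned difference.
- If the split is reversed (20%/40%), the bias is −0.10 SD, against the game.
- The zero row depends on a common gap. If only the lost intervention participants differ, 30%/30% loss with k = 0.5 gives 0.30 × 0.5 = 0.15 SD.

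**5. Effect on type I error.** This further assumes an SD of change of 1.03 and uses Φ(−1.96 + b/SE) + Φ(−1.96 − b/SE), where b is the bias.
- 40%/20%, k = 0.5: 114 and 152 completers; SE = 1.03 × √(1/114 + 1/152) = 0.128; b/SE = 0.81; error about 0.13.
- 35%/25%, k = 0.5: b/SE = 0.41; error about 0.07.
- Nominal: 0.05.

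**The case against.** The strongest reply is that much of this is inference, and several parts of that reply stand.

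- **An arm-specific reward.** A reader might infer that controls are rewarded with the game for answering at week 4. The article does not say so. It gives the timing of access and does not make access conditional on submitting the questionnaire. Only a difference in position between the arms remains.
- **No other answer to attrition.** A reader might infer that favouring adherers is the plan's sole response. It is not. Contact details are collected, non-responders are traced in both arms, the sample is inflated, and intention to treat is reported. Even so, 30% loss is still what the plan budgets for.
- **The intention-to-treat analysis as a completer analysis.** This follows if the named methods are applied to observed scores only, but the article states no exclusion rule. A missing-data method may sit in an analysis plan that is not shown, and its absence here is no fault. What the article does fix is the priority given to adherers.
- **A known bias toward the game.** A reader might take completers' effect D to stand for 0.70D over all randomised, an overstatement of 1/0.70 − 1 = 43%. That needs every lost intervention participant to be a non-player with no effect. Nothing in the article supports this, or any split such as 40%/20%.
- **The prize is tiny.** At US $0.20 in expectation, tying it to week 4 can be expected to yield only a modest gain in retention. This stands, and it makes the analysis change the more important of the two.

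**Conclusion.** The point holds in limited form. The article does state the 30% loss, a single outcome assessment, a draw with contradictory timing that is not linked to that assessment, and an analysis that answers attrition by prioritising adherent, exposed participants. Together with unblinded arms that differ in access to the game, these make bias possible.

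The article establishes neither the size nor the direction of that bias. Under the assumptions shown, it runs from zero (equal loss, common gap) to about 0.10 SD, roughly one fifth of the planned difference, at 40%/20% loss with a 0.5 SD gap. It changes sign if the controls are the ones lost. Overall power is not affected in any way that matters. The trial is described as preinitiation, so the changes can still be made.

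**What to change.** **1. Lottery.** Reconcile Sampling Method and Incentive into one draw held after data collection. Give an entry for submitting the week-4 questionnaire, identical in both arms and regardless of play. A second-entry version lets early leavers keep their first entry.

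Cost: the consent form and information sheet need rewording, and the budget can stay at about 4 prizes. In the second-entry version at 30% loss there would be 380 + 266 = 646 entries. Four prizes then give 4/646 = 0.6% per entry and about 1.2% for a completer, so the stated 1:100 chance must be reworded too. Keeping 1:100 per entry would instead need 646/100, or 6 to 7 prizes (about US $129).

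**2. Analysis.** In the section on the primary outcome analysis:
- Make the comparison of all randomised participants the lead analysis, with the adherent, sufficiently exposed group as supporting.
- Report loss by arm.
- Add a sensitivity analysis that imputes missing week-4 PRHS for intervention participants from the control arm, using baseline PRHS and the demographics already listed.
- Use game logs, if at all, only within the intervention arm. Controls are not meant to play before week 4, so the logs cannot serve as a predictor common to both arms.

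Cost: a few sentences of text and a little more analysis, with no new data collection.

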## Results

### Current Status

The status of the study is in preinitiation stage. Results are expected in February 2017. We will present results as percentages, observed means with 95% confidence intervals, mean difference and 95% confidence intervals, standardized regression coefficients, and *P* values. All analysis will be performed using SPSS for Windows.

### Ethical Considerations

The study will be conducted according to the principles outlined in the Declaration of Helsinki International Guidelines for Ethical Review of Epidemiological Studies (CIOMS, 1991 Geneva). Furthermore, the research and development approval has been obtained from Kyoto University Graduate School and Faculty of Medicine Ethics Committee, Japan, and Swaziland’s Ministry of Health Ethics and Scientific committee. Caution will be taken to protect participant’s privacy during the data collection, data handling, and data reporting.

## Discussion

### Overview

The risk of HIV infection is high among young people who practice risky sexual behavior, often they do not perceive their risk to be high, a phenomenon termed optimistic bias [11,27,28,34-36]. Some studies have reported that increased risk perception leads to subsequent increase in HIV protective behaviors, such as acceptance of HIV testing [37] or condom use [38]. The mechanism that increased perception leads to protective behavior is implicit in many behavioral theories as noted by Napper and colleagues [11]. Consequently, the joint United Nations Programme on HIV/AIDS (UNAIDS) guidance note on “social and behavior change programming” outlines risk perception as a thematic focus area for effective HIV prevention [39].

### Trial Implications

In line with the guidance form UNAIDS, this trial will provide a robust and rigorous evaluation of the efficacy of mobile serious games in increasing HIV risk perception in a resource limited setting such as Swaziland. Findings from this study will be made available to Swaziland authorities and stakeholders working to improve HIV prevention in Swaziland. We envision that the results of this study will be highly relevant to HIV prevention interventions in Swaziland and will inform future innovative strategies for HIV prevention. We are hopeful that our results will be generalizable to other settings in SSA. To our knowledge this is the first randomized control trial of a mobile serious games–based study to increase HIV protective behaviors in Swaziland and SSA; therefore, our findings will be a timely contribution to literature.

## Appendix

Multimedia Appendix 1 Intervention development.

Multimedia Appendix 2 Pre- and post-intervention questionnaire for the SGpriv trial.

Multimedia Appendix 3 Informed consent form.

Multimedia Appendix 4 Trial information sheet.

## Abbreviations

AIDS: acquired immune deficiency syndrome
eNSF: Extended National Multi-sectoral HIV/AIDS Framework for 2014–2018
HIV: human immunodeficiency virus
M: mean
PRHS: perceived risk of HIV infection scale
SSA: Sub-Saharan Africa
UNAIDS: United Nations Programme on HIV/AIDS
